### Anesthesia procedures and perioperative management

All patients enrolled in this trial will undergo general anesthesia. Intraoperative monitoring will include non-invasive blood pressure (NIBP), electrocardiography (ECG), pulse oximetry (SpO_2_), and bispectral index (BIS). Anesthesia will be induced with intravenous propofol (1.5–2.5 mg/kg), combined with sufentanil (0.2–0.4 μg/kg) for analgesia. Rocuronium (0.6–0.9 mg/kg) will then be administered to facilitate muscle relaxation. Following induction, endotracheal intubation will be performed, and tube placement will be confirmed. Mechanical ventilation will be initiated to maintain end-tidal carbon dioxide between 35 and 45 mmHg.

Anesthesia maintenance will consist of continuous infusions of propofol (2–4 mg/kg/h) and remifentanil (0.1–0.2 μg/kg/min), along with 1% sevoflurane. BIS values will be maintained between 40 and 60. Intraoperative hypotension (mean arterial pressure <65 mmHg or a ≥20% decrease from baseline) and bradycardia (heart rate <50 beats/min) will be treated as needed.

All patients will receive 8 mg of ondansetron to prevent postoperative nausea and vomiting. In the postoperative ward, if the VAS pain score exceeds 4, 50 mg of intravenous flurbiprofen axetil will be administered for analgesia.

### Data collection and monitoring

Patient data will be thoroughly reviewed by the research team using individual electronic medical records. The collected baseline variables will include age (years), sex, body mass index (BMI, kg/m^2^), education level, preoperative medications, comorbidities, American Society of Anesthesiologists (ASA) physical status classification, smoking status, and the time from injury to anesthesia induction, among others. Post-discharge information will be obtained via direct interviews or telephone follow-ups and recorded in the follow-up management system. In addition, major life events such as serious illnesses, accidents, or the death of close family members will also be documented.

All data will be recorded on case report forms (CRFs) and entered into a secure electronic database under the supervision of the principal investigator. An independent Data Monitoring Committee (DMC) will oversee the data collection process throughout the study. Upon completion of data entry, the database will be locked and anonymized datasets will be submitted to an independent statistician for final analysis according to the predefined statistical analysis plan.

Any serious adverse events (SAEs), whether related or unrelated to the study intervention, must be reported immediately to the principal investigator. Appropriate medical measures will be initiated by the perioperative care team to ensure patient safety. In addition, all SAEs will be reported to the DMC within 24 h for evaluation, including assessment of whether protocol modifications or study termination is required.

### Sample size calculation

According to the literature, the incidence of PTSD at 1 month after trauma surgery is approximately 23.2% (21). Previous epidemiological studies have reported rates up to 30–33% in patients with ocular trauma, substantially higher than in the general trauma population (9, 11). Based on these data and our small pilot observation, we set the expected PTSD incidence in the control group at 26%. We therefore adopted 26% as a conservative estimate to guide the sample size calculation. This conservative approach ensures that statistical power will not be underestimated if the true incidence in our study population is somewhat lower than that reported in epidemiological studies, while still remaining consistent with the published range. We hypothesize that SGB will reduce the risk of postoperative PTSD by 50% in patients undergoing emergency ocular trauma procedures. Using a two-sided test with a significance level of *α* = 0.05 and 80% power, a minimum of 142 participants per group is required. Accounting for an anticipated 10% dropout rate, the final target sample size is 300 patients, with 150 allocated to each group.

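### The 26% control rate is conservative only against the 30–33% ocular-trauma rates; at the cited 1-month rate of 23.2%, power with 135 evaluable per group is about 72%, not 80%

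*Protocol article*

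**What the plan says.** All of the following is in the protocol article, section Sample size calculation, unless noted.

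- A rate at the time point of the primary endpoint is cited for trauma surgery: "the incidence of PTSD at 1 month after trauma surgery is approximately 23.2"%.
- A second set of rates is cited for the injury under study, without a time point: "Previous epidemiological studies have reported rates up to 30–33% in patients with ocular trauma". The text calls these substantially higher than in general trauma.
- From these figures and a small pilot, for which the article gives no number, "we set the expected PTSD incidence in the control group at 26"%.
- This value is then labelled: "We therefore adopted 26% as a conservative estimate to guide the sample size calculation".
- The benefit claimed is: "This conservative approach ensures that statistical power will not be underestimated if the true incidence in our study population is somewhat lower". The sentence goes on to name its comparator, the incidence reported in epidemiological studies, which are the 30–33% figures.
- The effect is a 50% reduction in risk. The test is two-sided at 0.05 with 80% power, which gives 142 per group. With 10% dropout expected, the target is 150 per group.

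The primary outcome is PTSD at 1 month after surgery (Primary outcome). It is compared by chi-square test in randomized participants with available data (Statistical analysis), so patients lost to follow-up leave the primary analysis.

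**The concern.** When the effect is fixed as a relative reduction, a lower control rate means a smaller absolute difference, so more patients are needed. A planning value is therefore conservative only against rates above it. Of the two published sources cited in this section, one lies above 26% and one below, and the one below is the one that matches the endpoint's time point.

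The assurance about power also names the wrong error. If the true incidence is under 26%, the stated 80% is too high, so power has been overestimated. If the true incidence lies between 26% and the epidemiological rates, the stated 80% is too low, so power has been underestimated, which is what the sentence says cannot happen. On neither side of 26% does the sentence, as written, describe a useful safeguard.

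At stake is how a null result would be read. The passage invites the reader to treat the 80% as robust to a lower event rate, and no interim analysis is planned (Statistical analysis).

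**Working it through.** **Inputs.** Two-sided α = 0.05 (z = 1.960), power 80% (z = 0.842), 1:1 allocation, 50% relative reduction, 142 required and 150 randomized per group, 10% dropout (Sample size calculation); chi-square test on participants with data (Statistical analysis). Evaluable per group after the planned loss: 150 × 0.9 = 135.

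**Step 1. Reproduce the plan's own figure.** For 26% vs 13%, the unpooled normal formula is

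n = (1.960 + 0.842)² × [p₁(1−p₁) + p₂(1−p₂)] / (p₁−p₂)²
= 7.849 × (0.1924 + 0.1131) / 0.0169
= 7.849 × 0.3055 / 0.0169 = 141.9, so 142.

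This matches the stated 142. The pooled-variance version gives 145. The arithmetic behind 142 is sound.

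**Step 2. Same formula at the cited 1-month rate.** For 23.2% vs 11.6%:

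n = 7.849 × (0.1782 + 0.1025) / 0.116²
= 7.849 × 0.2807 / 0.013456 = 163.7, so 164 evaluable per group (167 with pooled variance).

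Dividing by 0.9 gives 183 to 186 randomized per group, against the planned 150.

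**Step 3. Power at 23.2% vs 11.6% with 135 per group.** By the unpooled formula:

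SE = √(0.2807/135) = 0.0456
0.116/0.0456 = 2.544
2.544 − 1.960 = 0.584
Φ(0.584) = 72.0%.

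The pooled formula gives 71.2%. Exact enumeration of the uncorrected chi-square test over the two binomial distributions gives 72.0%.

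**Step 4. Exact chi-square power over the cited range**, 50% relative reduction, 135 evaluable per group:

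| Control rate | SGB rate | Power |
|---|---|---|
| 23.2% | 11.6% | 72% |
| 26% | 13% | 78% |
| 30% | 15% | 85% |
| 33% | 16.5% | 89% |

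At 23.2%, power is about 74% with 142 per group and about 76% with all 150 analysed.

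**Step 5. Split the shortfall at 23.2%.** With 135 per group, moving from 26% to 23.2% takes exact power from 78.1% to 72.0%, about 6 points. The remaining 2 points or so (80% to 78.1%) arise at 26% itself, because 135 is below 142. To keep 142 evaluable after 10% loss, 142/0.9 = 157.8, so 158 per group would have to be randomized, not 150. That is a separate matter from the control rate.

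**The case against.** **The sentence is relative.** It speaks of an incidence lower than in the epidemiological studies, meaning 30–33%. Against those, planning at 26% is the more cautious choice, and if they apply, power is 85–89% even after dropout. This stands. A reader might infer that the protocol promises 80% power at any lower incidence. It does not say so. The fault is that *conservative* and *ensures* appear without a limit, in a paragraph that itself cites a rate below 26%, and that the error is named the wrong way round.

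**23.2% matches the time point but not the population.** It comes from trauma surgery generally, and the article holds that ocular trauma carries a higher risk. This also stands. A reader might infer that 23.2% is the right control rate and that the trial is therefore underpowered. The document supports neither step: 23.2% is a low-side reference within the cited range. Nor do the ocular rates settle the matter, since they are given as upper figures with no time point.

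**A pilot informed the 26%.** True, but the article gives no value for it, so it can neither confirm nor weaken the choice here.

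**Nothing is miscalculated.** Correct: 142 reproduces. The point concerns the property claimed for the design, not the sum.

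**The effect could be held on the absolute scale.** If a 13-point difference were kept (23.2% vs 10.2%), power with 135 per group would be about 82–83%. The protocol states its hypothesis as a 50% reduction in risk, so the relative scale is the one to use.

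**Conclusion.** The justification is wrong as written. The value of 26% lies between the cited rates: below 30–33% and above 23.2%. It is conservative against the former only. A lower incidence puts the stated power at risk of being overestimated, not underestimated. With 300 patients and 10% loss, power runs from about 72% at 23.2%, through 78% at 26%, to 85–89% at 30–33%.

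These figures assume a 50% relative reduction at every control rate, an uncorrected chi-square test, 135 evaluable patients per group, and no gain from covariate adjustment. The whole drop from 80% to 72% should not be charged to the control rate: about 6 points belong to it, and the rest belongs to the dropout inflation. Even with no loss at all, power at 23.2% is about 76%.

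**What to change.** In Sample size calculation:

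1. State that 26% lies between the cited 23.2% (general trauma surgery, 1 month) and 30–33% (ocular trauma, no time point), and that the pilot also informed it. Do not call it a midpoint: the midpoints are (23.2 + 30)/2 = 26.6% and (23.2 + 33)/2 = 28.1%.
2. Use *conservative* only for the comparison with 30–33%.
3. Delete the sentence that claims power is ensured against underestimation.
4. Replace the single 80% figure with power for 300 patients at 10% loss and a 50% relative reduction: about 72% at 23.2%, 78% at 26%, 85% at 30% and 89% at 33%.

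The cost is a few sentences and a four-row table. The sample size, the primary test and the conduct of the trial stay as they are. The price is a stated power less favourable than the present text suggests.

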### Statistical analysis

The normality of continuous variables will be evaluated using the Shapiro–Wilk test. Data following a normal distribution will be reported as mean (standard deviation, SD), while non-normally distributed data will be expressed as median (interquartile range, IQR). Group comparisons for normally distributed continuous variables will be conducted using independent t-tests or repeated measures ANOVA, as appropriate. For non-normally distributed variables, analyses will be performed using the Mann–Whitney U test or generalized estimating equations (GEE) to account for repeated measures and potential correlations. Categorical data will be presented as counts (percentages) and analyzed using the chi-square test or Fisher’s exact test, as appropriate, based on expected frequency distributions.

The 1-month postoperative prevalence of PTSD, defined as the primary endpoint, will be compared between groups using the chi-square (*χ*^2^) test. Group differences will be reported as odds ratios (ORs) with 95% confidence intervals (CIs). To control for potential confounders, logistic regression models will be used to obtain adjusted ORs. Subgroup analyses will also be conducted using logistic regression to examine treatment-by-covariate interactions.

Analyses of the primary outcome will primarily follow a modified intention-to-treat (mITT) approach, including all randomized participants with available data, regardless of protocol adherence. A per-protocol (PP) analysis will also be performed, excluding patients with major protocol deviations or who withdrew consent, to assess the treatment effect among fully adherent participants. No multiple testing correction is planned for secondary outcomes; these results will be interpreted as exploratory.

To evaluate CAPS-5 score changes over time (at 1- and 6-month follow-ups), repeated measures analysis will be performed using a covariate-adjusted linear mixed model (LMM). Fixed effects will include group (SGB vs. control), time (1 month vs. 6 months), and the group-by-time interaction. Potential confounding variables—such as sex, age, Injury Severity Score (ISS), laterality of ocular trauma (unilateral or bilateral), time from injury to surgery, and baseline VAS pain scores—will be entered as covariates. If significant time-by-covariate interactions are detected, they will be incorporated into the model. Results will be presented as least squares means (LSMs) with 95% CIs.

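### The target of 150 per group does not allow for the stated 10% dropout on the stated minimum of 142; at that loss, power is about 78%, not 80%

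*Protocol article*

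**What the plan says.** In the protocol article, under Sample size calculation, the control rate is fixed first: "we set the expected PTSD incidence in the control group at 26" per cent. The effect follows: "We hypothesize that SGB will reduce the risk of postoperative PTSD by 50" per cent, which puts the SGB group at 13%. The error rates are two-sided 0.05 and 80% power, and the result is that "a minimum of 142 participants per group is required". The next sentence gives the final target: "Accounting for an anticipated 10% dropout rate, the final target sample size is 300 patients, with 150 allocated to each group".

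The Statistical analysis section names a chi-square test of 1-month PTSD as the primary comparison. It is run on a modified intention-to-treat set, "including all randomized participants with available data, regardless of protocol adherence". Multiple imputation appears only among the sensitivity analyses.

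The total of 300, or 150 per arm, is repeated in the abstract, in Study design and patients, in Randomization and blinding, and in the Discussion.

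**The concern.** Two consecutive sentences disagree. One sets a minimum number per group. The other sets a recruitment target that is said to protect that minimum against 10% loss. Taking 10% off the target gives a number below the minimum.

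This affects the primary analysis directly, because a patient without a 1-month CAPS-5 result is not in it. Follow-up after discharge is by interview or telephone, so some loss is to be expected. At stake is the accuracy of the published justification for the sample size: a reader would credit the trial with 80% power at 10% dropout, which its own inputs do not give.

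**Working it through.** **Inputs** (all from Sample size calculation): control rate p1 = 0.26; 50% relative reduction, so p2 = 0.13 and the difference is 0.13; two-sided alpha 0.05 (z = 1.960); power 80% (z = 0.842); stated minimum 142 per group; dropout 10%; target 150 per group.

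**Step 1. Reproduce the stated minimum.** The unpooled normal formula is

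n = (1.960 + 0.842)² × [p1(1 − p1) + p2(1 − p2)] / (p1 − p2)²

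- Variance term: 0.26 × 0.74 + 0.13 × 0.87 = 0.1924 + 0.1131 = 0.3055.
- n = 7.849 × 0.3055 / 0.0169 = 141.9, rounded up to 142.

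This matches the protocol exactly, so the base figure is sound.

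**Step 2. Apply the dropout allowance.**

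| Calculation | Per group | Total |
|---|---|---|
| 142 / (1 − 0.10) = 157.8 | 158 | 316 |
| Weaker shortcut, 142 × 1.10 = 156.2 | 157 | 314 |
| Protocol target | 150 | 300 |

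Neither rule leads from 142 to 150. Against 158, the target is short by 8 per group, or 16 in total.

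**Step 3. Work back from the target.**

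- Remaining after 10% loss: 150 × 0.90 = 135 per group, and 142 − 135 = 7 below the minimum.
- Largest loss that still leaves 142: 1 − 142/150 = 5.3%.

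**Step 4. Power at 135 per group, 26% versus 13%.**

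- Standard error of the difference: √(0.3055/135) = 0.04757.
- 0.13/0.04757 = 2.733, and 2.733 − 1.960 = 0.773. The standard normal probability below 0.773 is 78.0%.

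Exact power was also found by summing binomial probabilities over all outcomes for which the uncorrected chi-square test is significant:

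| Analysed per group | Unpooled formula | Exact chi-square |
|---|---|---|
| 135 (10% loss) | 78.0% | 78.1% |
| 142 (stated minimum) | 80.0% | 79.9% |
| 143 | 80.3% | 80.2% |
| 150 (no loss) | 82.1% | 82.1% |

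The two methods agree to within about 0.2 points at every size shown.

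**The case against.** The best defence concerns size, not arithmetic. The loss is about 2 points of power, and uncertainty in the planning assumptions matters more. The same section cites control rates from 23.2% to 33%. With a 50% reduction and 135 per group, unpooled power runs from about 72% at 23.2% to about 89% at 33%, and a control rate of 27% brings it back to about 80%. This stands, and it limits how serious the point is. It does not reconcile the two sentences, because the protocol chose 26% and calculated from it.

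A reader might infer more than the document supports in three ways.

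- **That the chi-square test needs 145 per group, so 162 after dropout.** The pooled-variance approximation does give 145 (144.6 rounded up), and 145/0.9 = 161.1. But exact power of the uncorrected chi-square test is 79.9% at 142 and 80.2% at 143. The stated 142 is therefore right to within one patient per group, and the pooled formula understates power here.
- **That the trial is underpowered to the point that a null result could not be interpreted.** A 2-point shortfall does not support that. The protocol plans to report an odds ratio with a 95% confidence interval, which shows what a null result does and does not rule out.
- **That covariate adjustment would make up the difference.** The document gives no figure for the prognostic strength of any covariate, so no gain can be claimed.

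**Conclusion.** The sample-size statement is wrong as written. The target of 150 per group does not follow from 142 with 10% dropout: 135 would remain, and 158 would be needed. On the protocol's own assumptions, power at 10% loss is about 78% rather than 80%, and the target covers a loss of about 5%.

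This rests on 26% versus 13%, equal loss in both groups, a chi-square test without continuity correction, and a primary analysis confined to patients with outcome data. The contradiction between 135 and 142 needs none of the power calculations. It is a stated figure that should be corrected. It is not a flaw that threatens the design or the validity of the comparison.

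**What to change.** Replace the last sentence of the Sample size calculation section, for example with: *300 randomised patients (150 per group) give about 78% power for 26% versus 13% if 10% are lost; 80% power holds only if loss is at most about 5%.*

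This costs one sentence and a slightly less favourable power figure, and it changes nothing in the conduct of the trial. If the sponsor prefers to keep both 80% power and the 10% allowance, the target becomes 158 per group, 316 in total, at the cost of 16 more patients and of changing the total wherever it is repeated. Either choice removes the contradiction.

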### Statistical analysis

The normality of continuous variables will be evaluated using the Shapiro–Wilk test. Data following a normal distribution will be reported as mean (standard deviation, SD), while non-normally distributed data will be expressed as median (interquartile range, IQR). Group comparisons for normally distributed continuous variables will be conducted using independent t-tests or repeated measures ANOVA, as appropriate. For non-normally distributed variables, analyses will be performed using the Mann–Whitney U test or generalized estimating equations (GEE) to account for repeated measures and potential correlations. Categorical data will be presented as counts (percentages) and analyzed using the chi-square test or Fisher’s exact test, as appropriate, based on expected frequency distributions.

The 1-month postoperative prevalence of PTSD, defined as the primary endpoint, will be compared between groups using the chi-square (*χ*^2^) test. Group differences will be reported as odds ratios (ORs) with 95% confidence intervals (CIs). To control for potential confounders, logistic regression models will be used to obtain adjusted ORs. Subgroup analyses will also be conducted using logistic regression to examine treatment-by-covariate interactions.

Analyses of the primary outcome will primarily follow a modified intention-to-treat (mITT) approach, including all randomized participants with available data, regardless of protocol adherence. A per-protocol (PP) analysis will also be performed, excluding patients with major protocol deviations or who withdrew consent, to assess the treatment effect among fully adherent participants. No multiple testing correction is planned for secondary outcomes; these results will be interpreted as exploratory.

To evaluate CAPS-5 score changes over time (at 1- and 6-month follow-ups), repeated measures analysis will be performed using a covariate-adjusted linear mixed model (LMM). Fixed effects will include group (SGB vs. control), time (1 month vs. 6 months), and the group-by-time interaction. Potential confounding variables—such as sex, age, Injury Severity Score (ISS), laterality of ocular trauma (unilateral or bilateral), time from injury to surgery, and baseline VAS pain scores—will be entered as covariates. If significant time-by-covariate interactions are detected, they will be incorporated into the model. Results will be presented as least squares means (LSMs) with 95% CIs.

Sensitivity analyses will be conducted to evaluate the robustness of the findings. These will include complete case analysis and multiple imputation for handling missing data, additional covariate-adjusted regression models, and subgroup analyses to explore the consistency of treatment effects under different modeling assumptions.

As exploratory endpoints, Spearman’s or Pearson’s correlation analyses will be used to assess the relationships between preoperative VAS pain scores or Injury Severity Scores (ISS) and postoperative CAPS-5 scores.

All hypothesis testing will be two-sided, with a significance level of *p* < 0.05. For subgroup interaction terms, a threshold of *p* < 0.10 will be used to indicate potential effect modification. All statistical analyses will be performed using SPSS software (version 25.0; IBM Corp., Armonk, NY, United States). No interim analysis will be conducted.

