### Secondary outcomes

Secondary outcomes include the severity of PTSD, delayed-onset PTSD, the four core symptom clusters (intrusive re-experiencing, avoidance, negative alterations in cognition or mood, and hyperarousal/reactivity), and the severity of dissociative symptoms. Other secondary outcomes include Beck Anxiety Inventory (BAI) scores (range 0–84, higher scores indicating greater anxiety) assessed at 24, 48, and 72 h postoperatively; Visual Analog Scale (VAS) sleep scores (range 0–10, with 0 representing best and 10 worst sleep quality) at the same time points; and Numerical Rating Scale (NRS) pain scores (range 0–10, higher scores indicating more severe pain) also at 24, 48, and 72 h. Heart Rate Variability (HRV) will be assessed intraoperatively and again at 24 and 48 h postoperatively. Recovery time is defined as the interval from cessation of general anesthesia maintenance medication to recovery of consciousness, while extubation time is defined as the interval from cessation of anesthesia maintenance medication to extubation. The Richmond Agitation-Sedation Scale (RASS) will be used to evaluate patients’ level of consciousness, sedation, agitation, and their severity. Finally, the length of hospital stay will also be recorded as a secondary outcome.

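### A Shapiro–Wilk gate chooses the method for the repeated secondary outcomes (BAI, sleep, pain, HRV); one pre-specified mixed model, as already planned for CAPS-5, would be cleaner

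*Protocol article*

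**What the plan says.** All of the relevant rules are in the protocol article, Statistical analysis, unless another section is named.

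- **The gate:** "The normality of continuous variables will be evaluated using the Shapiro–Wilk test".
- **If normal:** "Group comparisons for normally distributed continuous variables will be conducted using independent t-tests or repeated measures ANOVA, as appropriate".
- **If not normal:** "For non-normally distributed variables, analyses will be performed using the Mann–Whitney U test or generalized estimating equations (GEE) to account for repeated measures".
- **CAPS-5 at 1 and 6 months:** here no gate applies. The article says "repeated measures analysis will be performed using a covariate-adjusted linear mixed model (LMM"), with group, time, their interaction and a list of covariates that includes the baseline VAS pain score.
- **Outcomes concerned (Secondary outcomes and Table 1):** BAI is "assessed at 24, 48, and 72 h postoperatively", and VAS sleep and NRS pain are taken at the same times. For HRV, "Heart Rate Variability (HRV) will be assessed intraoperatively and again at 24 and 48 h postoperatively".
- **Missing data:** among the sensitivity analyses, "These will include complete case analysis and multiple imputation for handling missing data". No outcome is named. The available-data (mITT) rule is worded for the primary outcome.
- **Status:** secondary results are not corrected for multiplicity and are to be read as exploratory.

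The gated rule speaks of continuous variables in general and does not name BAI, sleep, pain or HRV. That they fall under it follows from their being repeated continuous measures for which no other method is given.

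**The concern.** A rule that picks the method after a test on the outcome data does not fix the analysis in advance. Four consequences follow.

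1. **No single answer for a repeated outcome.** A score can pass the test at 24 h and fail at 72 h, or pass in one arm only.
2. **The quantity compared can change.** The t-test and ANOVA compare means; Mann–Whitney does not.
3. **GEE is in the wrong place.** It models the mean and accounts for correlation within patients, so failing a normality test is no reason to move to it. A failing outcome would be described by median and IQR and then compared by a contrast of means.
4. **Both repeated-measures branches handle missing visits less well than the model chosen for CAPS-5.** Classical repeated-measures ANOVA uses only patients complete at every visit. Unweighted GEE is generally valid only if data are missing completely at random. A likelihood-based mixed model uses every observation and is valid under the weaker missing-at-random assumption.

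At stake are the consistency and interpretation of four exploratory outcomes, and possibly some bias or loss of precision in them.

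**Working it through.** The documents state no figure on this point, so there is none to reproduce. The sample size of 142 per group belongs to the primary outcome and is not involved. The checks below rest on assumed inputs and show only how the rule behaves.

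**1. What the gate does (simulation, 150 patients, scale 0–10, normal scores clipped to the range, test at 0.05)**

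| Recording | Assumed mean, SD | Share rejected |
|---|---|---|
| Integers | (3, 1.5), (4, 2), (5, 2), (2, 1.5), (3, 1.8), (5, 1.8) | 100% in each |
| To 0.1 | (3, 1.5) | about 15% |
| To 0.1 | (4, 2) | about 11% |
| To 0.1 | (5, 2) | about 3% |
| To 0.1 | (2, 1.5), many values near the floor | near 100% |

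A skewed, BAI-like integer score (gamma, shape 2.5, scale 5) was also rejected in 100% of samples. The result thus turns largely on how finely the score is recorded and how close it lies to the floor. Neither says whether a model of the mean is adequate.

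**2. Branch "normal": complete-case loss under repeated-measures ANOVA**

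If each of three visits is missing independently with probability m, the complete share is (1 − m)³. The power column is for an assumed difference of 0.33 SD at one visit.

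| m | (1 − m)³ | Complete, of 150 per arm | Power |
|---|---|---|---|
| 0 | 1 | 150 | 81.5% |
| 2% | 0.98³ = 0.941 | 141 | 79.2% |
| 5% | 0.95³ = 0.857 | 129 | 75.4% |
| 10% | 0.90³ = 0.729 | 109 | 68.4% |

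If gaps arise only through drop-out before 72 h, the pattern is monotone. Then 10% missing at 72 h costs 10% of patients (150 × 0.90 = 135 remain), not 27%.

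**3. Branch "not normal": GEE against the mixed model**

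Inputs, all assumed: 150 per arm, 200 simulated trials, true difference −0.30 SD at each visit, within-patient correlation 0.6. About 17% are missing at 72 h, with the chance of being missing dependent on the observed 48 h score.

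| Estimate at 72 h | Same dependence in both arms | Opposite dependence by arm (extreme) |
|---|---|---|
| Full data, none missing | −0.31 | −0.30 |
| Complete cases | −0.28 | −0.10 |
| GEE, independence | −0.28 | −0.10 |
| GEE, exchangeable | −0.31 | −0.29 |
| Linear mixed model | −0.31 | −0.30 |

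Independence GEE with group, time and their interaction reproduces the observed means at each visit, hence its agreement with complete cases. Exchangeable GEE borrows from the earlier visits and stays close to the mixed model. The data were generated with an exchangeable correlation, which favours both of these. The bias of GEE therefore depends on the working correlation, which the article does not give.

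**The case against.** Several stronger readings are tempting, and the documents do not support them.

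- **That 14% or 27% of patients will be lost.** These are 1 − 0.857 and 1 − 0.729 from step 2. A score that always fails the gate goes to GEE, which uses all available observations, so it never meets the ANOVA loss. The loss applies only to an outcome that passes, and the arithmetic assumes independent gaps.
- **That early discharge makes missing values likely.** Table 1 places discharge after the 72 h column, and Data collection and monitoring provides for interviews or telephone contact after discharge. HRV could not be collected by telephone, but nothing shows that patients leave before 48 or 72 h.
- **That the gate always rejects.** This holds for integer recording. VAS sleep is given only as a 0–10 range; recorded to 0.1, rejection can be rare. HRV was not simulated, and no HRV index is named.
- **That GEE will mislead.** With an exchangeable working correlation it came within 0.01 of the mixed model. The choice of correlation may stand in the analysis plan that the article mentions and that is not at hand.
- **That missing data are ignored.** Multiple imputation is planned as a sensitivity analysis, and although these outcomes are not named, they are not excluded.

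All of this stands and limits the size of the point. It does not remove the core: the gated rule is written in the article, and the same section adopts a better method for CAPS-5.

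**Conclusion.** The point holds as a low-severity improvement. The article fixes a data-dependent rule for the method, and that is the only rule covering BAI, VAS sleep, NRS pain and HRV. Its two repeated-measures branches need either complete patients or a stronger missing-data assumption than the mixed model.

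The size cannot be stated. The documents give no missingness rate for 24–72 h, and with few missing values the effect on estimates is small. The simulated bias from −0.30 to −0.10 comes from a deliberately extreme assumption and is not a forecast. The outcomes are exploratory, and neither the primary analysis nor the CAPS-5 mixed model is affected. A reader should not infer that any conclusion of the trial is at risk.

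The verdict assumes that these four outcomes fall under the general rule for continuous variables, and that repeated-measures ANOVA means the classical form and GEE the unweighted form.

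**What to change.** For BAI, VAS sleep, NRS pain and HRV, drop the Shapiro–Wilk gate and pre-specify one likelihood-based linear mixed model of the kind planned for CAPS-5:

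- fixed effects for group, time and group-by-time, adjusted for the age stratum used in randomisation;
- a stated covariance structure, and all available observations included;
- residual checks, with a transformation or robust standard errors if they are needed.

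The baseline VAS pain score already named for the CAPS-5 model can be added as a covariate for postoperative NRS pain. A covariate need not be on the same scale as the outcome, so no change to data collection is needed.

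The cost is a change of analysis wording and slightly more programming in SPSS MIXED. Sample size, visits and the primary analysis stay as they are. The change should be made before the database is locked and anyone is unblinded.
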